
## Methods/Design

### Study Design and Setting

The CAN Stop study is a four-armed randomized wait-list controlled trial. Following Zwarenstein et al.'s [23] theoretical continuum of evaluation trials, on which rather "experimental", explanatory efficacy-oriented trials form the one end, and naturalistic, pragmatic effectiveness-oriented trials form the other end, this study tends towards the latter, pragmatic end. Developers were more interested in the real-life utility of the CAN Stop group training within the described four different contexts with their aforementioned specificities.

Data will be gathered at three points: before the group training (pre), after the group training (post; 3 months after pre) and at a follow-up (6 months after post). Modes of data retrieval vary from face-to-face interviews and questionnaires (pre), to questionnaires only (post) and telephone interviews and questionnaires (follow-up). Group comparisons will be made to check for the group training's effectiveness.

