In a first attempt to identify suitable cooperation partners, we systematically scanned comprehensive help provision and therapy guides of Northern and Eastern Germany as well as the Internet for institutions. All identified institutions were then invited to participate at the study with an information letter and asked to fax back an attached reply form together with a questionnaire about structural and work details of the institution, such as number of incoming young cannabis users in the targeted age range and number of staff. Prior to this, a target number of cooperation partners needed to gather the subjects was calculated on the basis of a power calculation, an estimated attrition rate of 50% and under the premise that CAN Stop training groups should be composed of six to ten group participants. If feedback was not given within six weeks after letters were sent out, a study group member called to check back with the institution. An exception from this procedure was made within the setting of juvenile prisons: because their total number was rather low, their staffs were contacted directly via phone calls. The response rate varied between different settings between 57% in juvenile prisons, 10% in in-patient medical clinics, 5% in out-patient medical clinics and 5% in the youth welfare and drug addiction aid. If institutions signalled to be in contact with young cannabis users in their daily routines and were interested in study participatioin, a study group member gave a presentation of the project and invited institutions to participate at the study. In sum, we could aquire a total of 11 cooperation partners within the youth welfare and drug addiction aid, 9 cooperation partners of the out-patient medical system, 8 cooperation partners of the in-patient medical system and 3 participating prisons for juvenile offenders. Participating cooperation partners were randomly assigned to perform the CAN Stop intervention plus their usual treatment as an intervention group or to provide for control group subjects, who received the cooperation partner's previously installed treatment as usual (TAU). As for other treatments, provided by the different institutions (besides CAN Stop), cooperation partners differed in their usually provided routines depending on their specific setting. While most prisons indicated, other kinds of therapy besides CAN Stop were rather limited and merely consisted of counselling talks or conceptual work within the organizational framework of the prison, the in-patient medical system's cooperation partners of course provided many other facets of treatment - to mention both extremes of this varying continuum. Institutions, which indicated they were already participating in other structured programmes similar to CAN Stop were excluded from the study in order not to compare CAN Stop with eventually competing studies (e.g. FrED, see above).

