### Measures

Young cannabis users participating at the study were asked to fill in several measures to assess target variables. Table 1 gives an overview of measures used.

**Table 1 T1:** Measures for young cannabis users

Target variable	Measure	Point of measurement
Sociodemographics Living situation Social network Problems with school, police, debts... Education Prior counselling and therapies		pre, follow-up
Screening for acute psychosis	Subscale of the Diagnostisches Interview psychischer Störungen (DIPS; Diagnostic Interview of psychiatric disorders) [26]	pre
Substance use history	Following the assessment standards III of the DG-Sucht (German Society for Addiction Research and Therapy)	pre, post, follow-up
Severity of dependence	Severity of dependence scale (SDS) [27]	pre, post, follow-up
Psychosocial adjustment	Youth self report (participants aged 14-17) [28] Young adult self report (Participants aged 18-21) [29]	pre, post, follow-up
Expected positive and negative effects of cannabis use	Comprehensive Cannabis Expectancy Questionnaire (CCEQ) [30]	pre, post, follow-up
Relationship to friends and peers	Questionnaire for health-related quality of life (Kiddo-KINDL revised, subscale "friends") [31]	pre, post, follow-up
Family relationships	Familienbogen/Selbstbeurteilungsbogen (family inventory, self-rating) [32]	pre
Motivation for change in cannabis use	Fragebogen zur Erfassung der Veränderungsbereitschaft (FEVER; Questionnaire to protocol the willingness for change) [33,34]	pre, post, follow-up
Personal goals with regard to changes in substance use	Zielskala [35]	pre, post, follow-up
Self-efficacy with regard to cannabis abstinence or limited cannabis use	Heidelberger Skalen zur Abstinenz-/Kontrollzuversicht (HEISA-16/HEIS-KOTZ-12; Heidelberg scales of confidence regarding abstinence/controlled use) [35]	pre, post, follow-up
Satisfaction with the training	Fragebogen zur Beurteilung der Behandlung, Version Patient (FBB-P; Questionnaire for the satisfaction with treatment, patient version) with minor adaptations [36]	post
Peer resistance regarding cannabis use	own development	pre, post, follow-up

In addition, trainers were asked to answer a short questionnaire about themselves prior to t0 in order to gather data for analysing possible trainer effects in secondary analyses. This included their professional background, own beliefs and attitudes towards cannabis use and personality characteristics, using the Big Five Inventory-10 (BFI-10) [25].

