### Analysis

An intention-to-treat approach will be taken to analyze data. Comparisons will be made between intervention group and the TAU control group in the different settings using baseline controlled ANCOVAs with cannabis use and abstinence-oriented self-efficacy as dependent variable and cannabis use at t0 as covariate. We plan to perform nested analyses in order to handle the variance, which is shared between participants attending the same institution. There are no institutions, which offer more than one CAN Stop training group, so a further layer of nesting is not nescessary. We hypothesize that intervention groups show lower levels of cannabis use and higher levels of self-efficacy related to cannabis-abstinence after the intervention as compared to controls. To discover these effects, we calculated the needed sample size of n = 119, assuming a medium effect size of f = 0.25, given the power of the statistical test to .80 and setting the α-error on .05. Prior experience with the target group have shown that attrition rates among young cannabis users are rather high, so we calculated with an attrition rate of 50% when planning the number of nescessary participants at t0. With regard to further effects, we believe there are differences in the effectiveness of the training in the different settings. We hypothesize that the effect of the training (d) will be greater when less other interventions take place in the respective setting, that is, effects are bigger in juvenile prisons and out-patient institutions than in in-patient setting clinics.

Secondary analyses will be made to compare the clientele of the different settings. Here we assume that more aggravated and chronic cannabis users will be found in prisons and in-patient settings than in out-patient settings. As for the role forced access to the group (e.g. because of pressure from juidical institutions or teachers) plays, we believe no differences will be seen between participants, who indicated, they were attending the intervention group because of pressure from outside, as compared to participants, who decided to attend the group solely on their own accord. This is, because we assume the CAN Stop training itself is shaped in a way as to leave decisions about further consume open to participants, which inspires the internal motivation of all participants and therefore blurs differences regarding forced access to the training.

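### A difference in training effect between out-patient and in-patient settings cannot be credited to the amount of other treatment: setting also carries expected severity, and other treatment is not recorded at t1

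*Protocol article*

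**What the plan says.** The Analysis section of the protocol article states a mechanism, that "the effect of the training (d) will be greater when less other interventions take place in the respective setting", and at once turns it into an ordering of settings: "effects are bigger in juvenile prisons and out-patient institutions than in in-patient setting clinics". The following paragraph, on secondary analyses, expects that "more aggravated and chronic cannabis users will be found in prisons and in-patient settings than in out-patient settings".

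On usual care, the section on recruitment of cooperation partners says that "cooperation partners differed in their usually provided routines depending on their specific setting". It describes other therapy as limited in most prisons and as extensive in in-patient clinics. It also reports 3 participating prisons and says that individual prisoners cannot be randomly allocated.

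On measurement, Table 1 has a row of background items ending in "Education Prior counselling and therapies", scheduled for pre and follow-up. No row records other treatment at post (t1). The severity of dependence scale (SDS) is collected at all three points. The only covariate named for the ANCOVAs is cannabis use at t0.

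**The concern.** The hypothesis is about how much other treatment people receive, but the planned comparison uses only the setting they come from. Randomisation concerns training against control. The four so-called arms are the settings themselves, and nobody is randomised to a setting. Any feature that differs between settings is thus a rival explanation for a difference in effect, and the plan names one such feature, severity.

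The comparison also lacks its natural check. The t1 contrast is CAN Stop plus usual treatment against usual treatment, yet what participants received besides CAN Stop between t0 and t1 is not asked at t1. The trial's second and third goals use setting comparisons to judge suitability and to guide later implementation. A statement that the training works best where little else is offered would go into that guidance without the data to support it.

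**Working it through.** The article gives no sample size or precision for this hypothesis, so there is no figure of its own to reproduce. Its n = 119 (f = 0.25, power 0.80, α 0.05) belongs to the training v control comparison. A noncentral F calculation for that comparison gives 128; an unstated covariate correlation of about 0.27 would give 119, since 128 x (1 - 0.27²) = 118.7. That is a separate matter, and nothing below depends on it.

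**Step 1: the two contrasts side by side.**

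| Contrast | Larger effect predicted in | Expected severity |
|---|---|---|
| Out-patient v in-patient | out-patient | in-patient higher |
| Prison v in-patient | prison | both in the more severe group |

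In the first row, less other treatment and lower expected severity go together. If greater severity weakens the training effect, both explanations predict the same result. If greater severity strengthens it, severity would mask an influence of other treatment. Either way the observed difference does not isolate other treatment. In the second row the plan expects no such severity ordering, so severity as the plan describes it is not a rival explanation. That contrast has other limits: 3 prisons split 2 v 1 at best, judicial allocation of individuals, and an official ban on use in prison.

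**Step 2: how large could the severity component be?** The documents give no figure. As an assumption, take a severity gap between settings of 0.3 to 0.8 SD and a change in d of 0.1 to 0.3 per SD of severity. The setting difference in d due to severity alone is gap x change:
- low end: 0.3 x 0.1 = 0.03
- high end: 0.8 x 0.3 = 0.24

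**Step 3: how precise is a setting comparison?** With n analysed per setting in equal arms and no clustering, Var(d) ≈ 4/n. The difference in d between two settings then has SE = √(8/n), and the difference detectable with 80% power is (1.96 + 0.84) x SE. The article does not say whether 119 is the total or the number per setting.
- 119 in total, about 30 per setting: SE = √(8/30) = 0.52, detectable difference 1.45
- 119 per setting: SE = √(8/119) = 0.26, detectable difference 0.73

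Clustering by institution would raise both.

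**Step 4: what is known about treatment received.** Post is 3 months after pre and follow-up is 6 months after post, so the next question on counselling and therapies comes 3 + 6 = 9 months after pre. It is answered only by those still in the study; the plan allows for 50% attrition without saying at which time point. Trainers at control institutions are trained in CAN Stop once their t1 measurements are complete, so care there may change between t1 and follow-up. Nothing in Table 1 shows that the follow-up answer can be separated into care before and after t1.

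**The case against.** The hypothesis sits among further effects, is worded at setting level and claims no power. Whether effects differ between settings can still be described, and the main ANCOVA is untouched. The Discussion says the authors want to know how differences between participants are reflected in the effects, SDS is collected, and the exact moderator model is ordinary analysis-plan content. All of this stands, and it limits the point to interpretation and one missing t1 item. It does not remove the point, because the article itself fixes the mechanism, the setting contrast and the measurement schedule.

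Three stronger readings are tempting, and the documents do not support them.

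- A reader might infer that nothing can be learned about background treatment. Prison v in-patient is not confounded by expected severity, and no source in the article says that severity reduces the training effect.
- A reader might infer that other treatment is wholly unknown. It is asked again at follow-up, which partly covers t0 to t1, and usual care is described at institution level for prisons and in-patient clinics.
- A reader might infer that uneven usual care between institutions biases the comparison of arms. The article says that institutions were randomly assigned and that nested analyses are planned, so chance differences belong in the standard error. A fall in usual care because staff now run CAN Stop is arguably part of the effect that a declared pragmatic trial estimates.

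**Conclusion.** The concern holds in a limited form. As planned, a difference in training effect between out-patient and in-patient settings cannot be attributed to the amount of other treatment alone, because setting is not randomised and the plan expects severity to differ along the same line. Prison v in-patient escapes this particular confounding but rests on 3 prisons without individual randomisation. Other treatment between t0 and t1 is not recorded at t1, and the follow-up item is late and limited to those retained.

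The direction and size of any severity effect are not known from the documents. The range of 0.03 to 0.24 in d rests entirely on the assumed gap and slope. It lies below the detectable setting difference under either reading of n = 119, so the data are unlikely to settle the question. That favours cautious wording over a claim about mechanism.

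**What to change.** 1. Add a short item to the t1 questionnaire in both arms on other cannabis-related counselling or therapy since t0, including help from outside the institution, and report it by arm and setting. It is measured after allocation, so use it for description and not as a covariate in the main comparison.
2. State that differences in effect between settings are descriptive and will not be read as evidence on the amount of other treatment.
3. Where the moderator is explored, include a training x baseline SDS term alongside training x setting. SDS as a main effect only would not remove effect modification by severity.
4. Optionally, score each institution's usual-treatment intensity, as exploratory only. Such a score is also not randomised and follows setting closely, and the article does not show that the institution questionnaire measured it.

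The cost is a few lines on an existing form and a change of wording. The moderator analysis remains imprecise with 11 + 9 + 8 + 3 = 31 institutions.

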
Recruitment for subjects was performed by cooperation partners within their daily work routines. In addition, the study group provided for flyers, which gave information on the study, its objectives and the group training to recruit participants. Young cannabis users interested in the programme were asked to contact a centralized telephone hotline installed by the study group to provide for a first check-up of inclusion criteria, to inform about the study and then to randomly allocate subjects to wait list control groups or to intervention groups in respective institutions. Young cannabis users in prisons are exempted from this procedure, because a random allocation of prisoners is not possible: the juidical allocation of young offenders into the prisons will decide about whether they are selected into a prison performing an intervention or a control group, their inclusion criteria are checked in in-take talks. Inclusion criteria were (1) the participants' age between 14 and 21 years, (2) a cannabis consume, which is deemed problematic by the young cannabis user or significant persons in his or her context (e.g. parents, teachers) (3) the participant's willingness to at least think over previous consumption patterns and to participate at a group dealing with the topic and (4) the informed consent of participants and in the case of underage participants the informed consent of a parent or official guardian. Young cannabis users were excluded from the study when they showed acute symptoms of psychosis or suicidality. Both of these exclusion criteria were checked via standardized screening questions at the beginning of the face-to-face take-in talks at the respective cooperation partner's institutions. Young cannabis users were invited to participate at the study regardless of whether their access to cooperating institutions was initiated by the cannabis users themselves or whether pressure was exerted by e.g. school, employers or because of a judicial condition of probation, however, this is documented and will be integrated into outcome analyses.

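### The expectation that pressured and voluntary clients will not differ is framed within the intervention group alone, which cannot show that the training evens out the two and is too small to support a finding of no difference

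*Protocol article*

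**What the plan says.** The hypothesis stands in the secondary-analysis paragraph of the Protocol article, Analysis: "we believe no differences will be seen between participants, who indicated, they were attending the intervention group because of pressure from outside". The comparator is the voluntary attenders, so both sides of the comparison lie inside the intervention group. The reason given is that the training leaves decisions about further use to the participant, which builds internal motivation in everyone and so removes the influence of how they came to the group.

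Under Recruitment of cooperation partners and young cannabis users, clients may join whether they come by themselves or under pressure from school, employers or a probation condition. Of the access route the article says "this is documented and will be integrated into outcome analyses".

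The only power statement concerns intervention against treatment as usual (TAU): "we calculated the needed sample size of n = 119". Its inputs are f = 0.25, a power of 0.80 and an alpha of 0.05. The article gives no expected share of pressured clients and no power for the access-route question.

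**The concern.** There are two difficulties, and the first does not depend on sample size.

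1. To say that the training removes a difference is to say something about effect modification. It needs the pressured-versus-voluntary difference under training and the same difference under TAU. The stated contrast supplies only the first.
2. The expectation is one of no difference, examined in a part of a sample that was sized for another question. A non-significant result there is weak evidence of similarity.

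At stake is how the programme is described for clients who come under outside pressure. The article's third goal is to draw conclusions for future use in the different settings, and a statement that access route makes no difference could feed into that.

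**Working it through.** **What the contrast can show.** Let D(train) be the mean outcome of pressured minus voluntary clients under training, and D(TAU) the same under usual treatment. The difference in training effect between the two kinds of client is D(train) − D(TAU). The stated contrast estimates D(train) only.

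- D(train) = 0 and D(TAU) = 0: the contrast is null, but the training removed nothing.
- D(train) = 0 and D(TAU) ≠ 0: the contrast is again null. Here the training did remove a difference, and its effect therefore differs by access route.
- D(train) = D(TAU) ≠ 0: the contrast shows a difference, yet the training works equally well in both.

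The first two cases look identical within the intervention group. The third looks like a failure of the hypothesis although effectiveness is equal.

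**The plan's own figure.** For two groups with f = 0.25 (d = 0.5), two-sided alpha 0.05 and power 0.80, the noncentral F calculation gives N = 128, and 119 gives 77.2% power. The stated 119 follows if a baseline correlation of about 0.26 is assumed: 128 × (1 − 0.26²) = 119.3. This is a separate matter and does not decide the present point. I take 119 as given.

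**How many are in the intervention group.** The article does not say whether 119 is a total, per group or per setting. With the stated 50% attrition, a total of 119 means 119 / 0.5 = 238 at t0. Over 11 + 9 + 8 + 3 = 31 institutions that is 7.7 each, which fits the premise that "CAN Stop training groups should be composed of six to ten group participants" with at most one group per institution. Reading 119 as per setting needs 4 × 238 = 952 at t0, about 31 per institution, which does not fit. I therefore assume an analysed total of 119 and 1:1 allocation, so about 60 in the intervention group.

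**Precision and power of the stated contrast.** The share of pressured clients is not given, so I show splits from 30/30 to 48/12.

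- 95% half-width in SD units = 1.96 × √(1/n₁ + 1/n₂). For 30/30: 1.96 × 0.258 = 0.51. For 48/12: 1.96 × 0.323 = 0.63.
- Power for d = 0.5: noncentral t with noncentrality 0.5 × √(n₁n₂/(n₁+n₂)) and 58 degrees of freedom. The noncentrality is 1.94 for 30/30 and 1.55 for 48/12.
- Clustering: assumed intraclass correlation 0.05 and 5 analysed per institution, so a design effect of 1 + 4 × 0.05 = 1.2. This applies in full only if access route hardly varies within an institution, so it is an upper value.
- Baseline adjustment: assumed correlation 0.5, with 0.5 SD on the unadjusted scale, so d becomes 0.5 / √(1 − 0.25) = 0.577.

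| Split | 95% half-width (SD) | 0.5 SD missed | Missed, with clustering | Missed, with baseline adjustment |
|---|---|---|---|---|
| 30/30 | 0.51 | 52% | 59% | 41% |
| 36/24 | 0.52 | 54% | 60% | not run |
| 42/18 | 0.55 | 58% | 64% | 48% |
| 48/12 | 0.63 | 67% | 72% | 58% |

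At 30/30 a true 0.3 SD difference is missed in about 79% of trials (normal approximation: 0.3 / 0.258 = 1.16, against 1.96).

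**If 119 were the intervention group alone,** the miss rate for 0.5 SD would be 23% to 42% over the same splits, without clustering.

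**Precision of the two-group interaction.** With four equal cells of 119/4, SE = √(16/119) = 0.37 SD, so the 95% half-width is about 0.72 and the 90% half-width about 0.60. With a 48/12 split in both groups, SE = √(2 × (1/48 + 1/12)) = 0.46 and the 95% half-width is about 0.89.

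**The case against.** A reader might infer that the plan will confirm its hypothesis by a non-significant test. The article does not say so. It states an expectation and a rationale and gives no test, margin or decision rule. In a condensed article these may properly be left to an analysis plan that is not shown, so their absence is no fault, and the point here is only that the result could be misread.

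A reader might also infer that the control group will play no part. That goes too far. Access route is recorded for study participants generally and is to enter the outcome analyses, and the main outcome analyses compare intervention with TAU. What stands is that this sentence promises no interaction, while the hypothesis itself is worded within the intervention group.

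The figures can fairly be called soft. They rest on an assumed total, allocation and split, and at an even split a miss rate of 52% is close to a coin toss. Baseline adjustment could bring it down to 41%. This weakens any claim that a false null result is likely. It does not make a null result informative, and it leaves the first difficulty untouched.

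Finally, the remedy will hardly settle the question. With a 90% half-width of about 0.60 SD, an equivalence rule with a margin of 0.3 or 0.5 SD could not be met. That is right, and it is why the comparison should be labelled exploratory and not turned into an equivalence test.

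**Conclusion.** The point holds in a limited form. As worded, the comparison cannot support the explanation attached to it, because that explanation concerns a difference in training effect and only one treatment group is compared. This needs no numerical assumption.

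The second part is conditional. On the reading of 119 that best fits the 31 institutions, a medium true difference would be missed in roughly 41% to 72% of trials across the splits, baseline adjustment and clustering considered. A null result would therefore say little about similarity.

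The severity is minor. The hypothesis is secondary, it is not among the five listed project goals, and neither the main comparison nor the sample size depends on it.

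**What to change.** Restate the hypothesis as one about the training effect, and add a group-by-access-route interaction to the baseline-adjusted, nested model that compares intervention with TAU. Report the interaction with its 95% confidence interval, together with the training effect in pressured and in voluntary clients. Label the analysis exploratory, and state beforehand that a non-significant interaction will not be read as equal effectiveness. Access route is not randomised, so the interaction describes whether the effect differs by route and not why.

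No new data should be needed, since access route is already to be documented for study participants. The cost is a change of wording and a more cautious conclusion: on the same assumptions the interval will be about ±0.72 SD or wider before baseline adjustment, so the result will probably be reported as inconclusive.
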